### Tertiary outcomes

Parental opinion that their child has atopic eczema at any point during the trial.Data on tertiary outcomes 2–5 are collected at 36, 48 and 60 months:Parental report of a clinical diagnosis of atopic eczemaSeverity of atopic eczema (POEM)Presence of other atopic diseases:
 Parental-reported wheezing, allergic rhinitis and food allergy symptoms Parental report of a clinical diagnosis of asthma, allergic rhinitis or food allergy Health-related quality of life (child; CHU-9D and parent; EQ-5D-5 L)
Health economic outcomes:
 Disease-related health care resource use Cost-effectiveness and cost-utility (combining health resource use and health-related quality of life outcomes)

### Randomisation, allocation concealment and blinding

The randomisation schedule (1:1 ratio) is based on a computer-generated pseudo-random code using random permuted blocks of randomly varying size. It was created by the Nottingham Clinical Trials Unit (NCTU) and is held on a secure University of Nottingham server. During the trial, access to the sequence is confined to the IT programmer at NCTU. Randomisation is stratified by recruiting centre and number of immediate family members (parents or siblings) with atopic disease (1, 2, or more than 2). Recruiting centre staff randomise participants via a web-based randomisation system developed and maintained by NCTU. Recruiting centre staff are not sent the results of the randomisation. It is not possible to blind parents as to which group they are in, but the trial nurses conducting the skin examination at the 2-year visit are blinded to treatment allocation.

### Study procedures and data collection

The screening and consent visit take place either in the family home or at the recruiting site, depending on parent preference, and consent obtained by the trial nurse (Figs. 2 and 3). Separate optional consent is obtained for the *FLG* genotyping, skin-prick testing and food challenges. Randomisation takes place after the infant is born and post-birth eligibility checks are completed. Parents are sent questionnaires online (or paper if requested) at 3, 6, 12, 18, 36, 48 and 60 months to collect outcome data. There is a second face-to-face visit with the trial nurse at 24 months, again in the family home or at the recruiting centre depending on parent preference. At this 24-month visit the blinded trial nurse conducts the skin examination for the diagnostic criteria and the EASI, completes the questionnaires, and (where consent is given) takes the saliva sample and carries out the skin-prick test. A summary of the data collection can be found in Table 1: The schedule of trial assessments. The trial nurses are fully trained in the diagnosis of atopic eczema and carrying out the EASI.

Saliva samples are collected via the child spitting into a pot or swabs taken from the inside of the child’s cheek and sent to the Centre for Dermatology and Genetic Medicine, University of Dundee for deoxyribonucleic acid (DNA) extraction by standard techniques and *FLG* genotyping for the most prevalent null mutations in the white European population (2282del4, R501X, S3247X and R2447X) according to published protocols [31]. The skin-prick testing is carried out in line with the British Society for Allergy and Clinical Immunology procedures [32] and the following allergens are tested; grass pollen mix, dust mite and cat (Allergopharma, Germany), peanut (Inmunotek, Spain), fresh skimmed cow’s milk and fresh chicken egg. Positive (1% histamine) and negative (0.9% saline) controls will also be used (Allergopharma, Germany). The trial nurses are fully trained in conducting skin-prick tests and emergency procedures in the highly unlikely event of any serious allergic reactions. Participants with a positive skin-prick test or history suggestive for food allergy in whom further investigation is required for a diagnosis of food allergy to be made are invited for a supervised oral food challenge conducted by experienced allergy nurses following standard procedures who are blinded to treatment allocation. The presence of a clinical reaction is determined using modified PRACTALL and iFAAM criteria [33, 34].

A methodological two-by-two factorial substudy is nested within this trial to investigate the effectiveness of interventions designed to improve rates of follow-up data collection. The interventions are SMS text message notifications that the questionnaires will be sent by email or post the following day versus no text message and the £10 inconvenience voucher either sent to parents either before the visit, or given at the 24-month visit. Full details can be found in the Studies Within A Trial (SWAT) registry [35].

Small tokens of appreciation and birthday cards are sent to all participating families throughout the trial to promote retention, and the trial coordinating centre will make every effort to keep the parents contact details up to date throughout the trial. When questionnaires are not completed online or by post, families are telephoned by trial coordinating centre staff. Families wishing to withdraw from the intervention are encouraged to continue to provide data on the main outcomes, with particular importance placed on the 24-month face-to-face visit where the primary outcome data is collected. Where a face-to-face visit is not possible (e.g. the family have moved abroad) key outcomes are collected via remote means (e.g. telephone, text, email or post).

Data will be entered directly onto the database by the trial nurses or parents via online questionnaires. All data are treated confidentially and held on a secure University of Nottingham server with restricted and password-protected access. Questionnaires and other data collection forms will be available as part of the final trial report.

### Sample size calculation

The sample size calculation was carried out using Stata [36, 37]. A total of 1282 infants are required to detect a relative reduction of 30% in the intervention group in the number of infants who developed atopic eczema in the previous year (between 12 and 24 months of age) at the 5% significance level (two-sided) with 90% power based on an expected rate of 30% in the control group and allowing for 20% attrition at 24 months. This relative reduction is considered a conservative estimate; results of the pilot study showed a 50% reduction in atopic eczema at 6 months (43% developed atopic eczema in the control group (*n* = 55) compared to 22% in the emollient group (*n* = 53), 95% CI 0.28 to 0.9) [21]. The effect size is anticipated to be lower in this main trial than in the pilot due to the more pragmatic trial design and the longer-term outcome assessment.

Recruitment began in November 2014 and ended in November 2016. A sample size review by the TSC took place after 21 months of recruitment to check the atopic eczema rate in the control group and attrition. As recruitment had progressed better than expected, the TSC advised that no additional families should be consented to the trial, but those who had already consented to the trial should continue to be randomised. The total number randomised at that point was expected to be approximately 1400.

### Planned analysis

Analysis of the primary, secondary and safety outcomes will be performed when all the 24-month data have been collected. The longer-term tertiary outcomes will be analysed once data collection is complete for the 60-month follow-up.

The main approach to all analyses will be to analyse participants as randomised (intention-to-treat), regardless of adherence with allocation and without imputation for missing data. All analyses will be carried out using Stata/SE 13 or above [36].

The primary outcome will be analysed using a generalised linear model adjusting for stratification variables. The difference between the two groups will be summarised using a relative risk with 95% confidence intervals. Sensitivity analyses will be performed using multiple imputation for missing outcomes by including any prognostic variables showing a baseline imbalance in the model and accounting for actual emollient use. Analyses of secondary and long-term outcomes will use appropriate regression models depending on the type of outcome and differences between the two groups summarised with 95% confidence intervals. Descriptive analysis of safety endpoints will be presented both according to randomised group and according to actual emollient use in the two groups. Planned subgroup analyses will be conducted by including an interaction term in the regression analysis for the primary outcome according to: (1) whether an individual is *FLG-*wild-type genotype or whether they have one or two of the screened *FLG* null mutations, (2).the number of immediate family members with atopic disease and (3) the number of immediate family members with atopic eczema.

Full details of the analyses and potential sensitivity analyses for the food allergy/sensitisation outcomes will be documented in the Statistical Analysis Plan prior to any analysis and made publicly available on the trial website [23].

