### Secondary outcomes

The secondary outcomes relate to outcomes up to and including the 24-month time point:Presence of atopic eczema between birth and 24 months defined as:
 Parental report of a clinical diagnosis of atopic eczema Parental completion of UK Working Party Diagnostic Criteria for Atopic Eczema at 12 and 24 months (Additiona﻿l file 2)
Presence of visible atopic eczema at 24 months (assessed by a trained research nurse blinded to treatment allocation)Time to onset of atopic eczema:
 First parental report of a clinical diagnosis of atopic eczema First topical corticosteroid and/or immunosuppressant prescription for atopic eczema
Severity of atopic eczema:
 Eczema Area and Severity Index (EASI) (Additional f﻿ile 3) at 24 months and Patient-oriented eczema measure (POEM) (Additional file 4) at 12 and 24 months. EASI and POEM are the core outcome instruments recommended by the Harmonising Outcome Measures for Eczema (HOME) for measuring clinician-reported signs and patient-reported symptoms respectively [27, 28] and are both well validated [29, 30]. The EASI will be completed by a trained research nurse who is blinded to treatment allocation
Presence of other allergic diseases:
 Parental-reported wheezing, allergic rhinitis and food allergy symptoms, and parental report of a clinical diagnosis of food allergy between 12 and 24 months Allergic sensitisation at 24 months to any of the following common allergens: milk, egg, peanut, cat, grass pollen, house dust mite Confirmed diagnosis of food allergy at 24 months to milk, egg, and/or peanut derived from a combination of parental report, allergic sensitisation and (if required) food challenge
Health-related quality of life:
 Child quality of life using the Child Health Utility 9D (CHU-9D) at 24 months Parental quality of life measured using the EuroQol-5D-5 L (EQ-5D-5 L) at baseline and 24 months
Health economic outcomes:
 Disease-related health care resource use Cost-effectiveness and cost-utility at 24 months (combining health resource use and health-related quality of life outcomes). If significantly more effective than usual care at 24 months, a longer-term economic model from birth to 16 years we be developed

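### The missing-data sensitivity analysis picks variables by observed baseline imbalance, a poor rule on either reading of the sentence, and gives little check if dropout depends on arm and on eczema seen so far

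*Protocol article*

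**What the plan says.** All references are to the protocol article.

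- **Main analysis (Planned analysis).** Participants are analysed as randomised, "regardless of adherence with allocation and without imputation for missing data". The primary model is a generalised linear model adjusted for the stratification variables, summarised as a relative risk.
- **Sensitivity analyses (same section).** "Sensitivity analyses will be performed using multiple imputation for missing outcomes by including any prognostic variables showing a baseline imbalance in the model". The sentence then adds, without punctuation, that actual emollient use will be accounted for. It names no method for that.
- **Attrition (Sample size calculation).** The target of 1282 allows for 20% attrition at 24 months.
- **Eczema data before and at 24 months.** Under Study procedures and data collection: "Parents are sent questionnaires online (or paper if requested) at 3, 6, 12, 18, 36, 48 and 60 months to collect outcome data". Secondary outcomes include parental report of a clinical diagnosis, POEM at 12 and 24 months, and "Parental completion of UK Working Party Diagnostic Criteria for Atopic Eczema at 12 and 24 months".
- **Deferral.** The article is an abridged protocol, and Planned analysis leaves full details to a statistical analysis plan (SAP), which was not available here.

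**The concern.** A complete-case analysis is unbiased only if those with a missing outcome resemble those observed, within arm and adjustment stratum. Parents know their allocation. A family in the emollient arm whose child has developed eczema may be more, or less, likely to attend at 24 months than a comparable control family. If so, dropout depends on arm and on eczema seen so far, and the complete-case RR is biased.

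Imputation helps only through variables that predict both the outcome and its missingness. Chance imbalance between arms at baseline is neither. A variable can be imbalanced and nearly useless for imputation, or perfectly balanced and very informative. If the imputation rests on the imbalanced baseline variables, it will tend to agree with the complete-case result whether or not that result is biased, and the agreement could be taken for reassurance.

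If the sentence instead describes a separate covariate-adjusted analysis, the fault is smaller but still present. The covariate list would depend on the observed data and would leave out balanced prognostic variables.

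**Working it through.** **1. The plan's own figure.** The inputs are "at the 5% significance level (two-sided) with 90% power based on an expected rate of 30% in the control group", a 30% relative reduction (so 0.21 in the intervention arm), 1:1 allocation and 20% attrition.

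n per arm = [1.960·√(2·0.255·0.745) + 1.2816·√(0.30·0.70 + 0.21·0.79)]² / 0.09² = 490.8

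With continuity correction: (490.8/4)·[1 + √(1 + 4/(490.8·0.09))]² = 512.8

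2 × 512.8 / 0.80 = 1282, as stated. The sample size is not in question. At 20% attrition, about 256 of 1282 or 280 of 1400 primary outcomes would be missing.

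**2. Complete-case bias in closed form (assumed inputs).** The article gives no missingness pattern and no accuracy for parent report, so the following are assumptions except the 30% control risk.

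Let p be the true risk in an arm. Let s be the proportion of later cases with early parent-reported eczema, and f the same proportion among non-cases. Let m₁ and m₀ be the proportions of outcomes missing with and without such a report.

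- Proportion of cases observed: a = 1 − [s·m₁ + (1−s)·m₀]
- Proportion of non-cases observed: b = 1 − [f·m₁ + (1−f)·m₀]
- Observed risk = p·a / [p·a + (1−p)·b]

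*Illustration A:* s = 0.75, f = 0.20. Controls have 20% missing regardless of report. The emollient arm has m₁ = 0.35 and m₀ = 0.14.

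- Emollient arm: a = 1 − (0.2625 + 0.035) = 0.7025; b = 1 − (0.07 + 0.112) = 0.818.
- True RR 1.00 (p = 0.30): 0.21075 / (0.21075 + 0.5726) = 0.269, so complete-case RR = 0.269/0.30 = **0.90**. Missing in this arm: 21.7%.
- True RR 0.80 (p = 0.24): 0.1686 / (0.1686 + 0.62168) = 0.213, so complete-case RR = **0.71**.

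Within arm and report stratum, missingness here is random, so imputation that uses the report recovers the truth. For p = 0.30, the stratum with a report is 0.365 of the arm with risk 0.225/0.365. The stratum without is 0.635 with risk 0.075/0.635. Recombined: 0.225 + 0.075 = 0.30, so RR = 1.00.

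*Illustration B:* true RR 0.70, report sensitivity 0.80 and specificity 0.85. The complete-case column follows from the formulas above. The imputation columns come from a simulation of 2 million records that also included a three-level family-history variable as baseline predictor.

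| Missing without / with reported eczema | Complete case | Imputed: arm + baseline | Imputed: + parent report |
|---|---|---|---|
| 20%/20% in both arms | 0.70 | 0.70 | 0.70 |
| 15%/30% in both arms | 0.69 | 0.69 | 0.70 |
| Control 20%/20%, emollient 15%/35% | 0.61 | 0.61 | 0.70 |
| Control 24%/12%, emollient 15%/30% | 0.59 | 0.59 | 0.70 |

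Worked last row. Control: a = 0.856, b = 0.778, risk 0.2568/0.8014 = 0.320. Emollient: a = 0.73, b = 0.8275, risk 0.1533/0.8070 = 0.190. Ratio 0.59.

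Imputing from arm and baseline risk never moved the RR by more than about 0.002 from complete case.

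**3. Adding emollient use to the imputation (simulation, 3 million records).** Where use was unrelated to outcome and dropout, adding it changed nothing: 0.595 before and after, against a full-data 0.700. Where use predicted both, it did help: from 0.465 to 0.478 (full-data 0.559) in one scenario, and from 0.535 to 0.557 (full-data 0.557) in another.

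**The case against.** The strongest reply is that the sentence is condensed and ambiguous. It can equally be an unpunctuated list of imputation, extra covariate adjustment and an adherence analysis. On that reading the imputation inputs are simply not stated, and the content of an imputation model is commonly left to the SAP. This stands, and it limits the point in several ways.

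- A reader might infer that the imputation inputs are settled and that parent-reported eczema is left out. The article does not support that: it names no such variable for imputation, but it excludes none and defers the detail.
- A reader might infer an as-treated efficacy analysis. None is stated. A breakdown by actual use is described only for the safety endpoints, and the wording on emollient use is compatible with a randomisation-based method.
- A reader might infer that imputation is the trial's only protection against missing data. It is not. Non-responders are telephoned, key outcomes are collected remotely when a visit is impossible, families who stop the intervention are encouraged to keep providing data, and parents complete the same criteria at 24 months.
- A reader might infer that the check is bound to repeat the complete-case result. That was shown for arm plus baseline inputs, not once emollient use is added (step 3). Using a post-randomisation variable in an imputation model is not in itself a fault.

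It is also fair to note that the rule asks for variables to be prognostic as well as imbalanced. That improves it, but the imbalance condition still discards prognostic variables that happen to be balanced.

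What the reply does not remove is the selection rule. It is stated text, not a gap, and a SAP that elaborates this sentence would inherit it.

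**Conclusion.** The point holds in a limited form. Choosing variables by observed baseline imbalance is a poor rule on either reading: the wrong criterion for an imputation model, and a data-driven one for covariate adjustment.

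The consequence is conditional. Under assumed missingness that depends on reported eczema differently by arm, the complete-case RR was off by about 0.1, roughly a third of the 30% relative reduction the trial is sized to detect, and imputation from baseline variables did not reveal it. With random missingness the error was nil, and with the same dependence in both arms about 0.01.

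Two assumptions favour the remedy. The illustrations let missingness depend only on arm and parent report, and they take the report as available for every infant without a 24-month outcome. If families stop returning questionnaires, or dropout depends on eczema that was never reported, recovery would be incomplete. The near-identity of baseline imputation and complete case also assumes that the baseline variables do not themselves drive dropout strongly.

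The sample size and the primary analysis are unaffected.

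**What to change.** Split the sentence, in the SAP or at the next protocol revision, into three separately labelled sensitivity analyses.

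1. **Multiple imputation of the missing primary outcome, by arm.** Choose variables because they predict the outcome and its missingness: the stratification factors, parent-reported diagnosis at the 3, 6, 12 and 18 month questionnaires, and the parent-completed diagnostic criteria and POEM at 12 months, and at 24 months where returned.
2. **Covariate adjustment** for a list of prognostic baseline variables fixed in advance, without reference to observed imbalance.
3. **Adherence**, as its own analysis with a named method, preferably one that rests on randomisation, such as a complier-average causal effect.

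The cost is a rewritten paragraph and a little more analysis. All the variables are already collected, so no new data are needed.

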### Economic evaluation

Economic evaluations will be conducted to estimate the cost-effectiveness of the intervention from an NHS perspective in the short term (24 months within trial analysis), medium term (60 months within trial analysis) and, if appropriate, longer term (birth to 16 years using a model-based analysis). For the within trial analyses, the incremental cost per atopic eczema case prevented, incremental cost per quality-adjusted life year (QALY) based on CHU-9D (parental-proxy reported), and incremental cost per QALY based on main carer own health-related quality of life (EQ-5D-5 L) will be estimated. An incremental cost-effectiveness analysis will be performed using accepted methods with data reported in a disaggregated way [38–41]. Analysis of uncertainty will follow recommended practice with results presented as cost-effectiveness acceptability curves [42, 43]. If the intervention is significantly more effective at 24 months than normal practice, a longer-term economic model taking an NHS perspective will be developed for the economic costs and benefits of the intervention for a single birth cohort from birth to 16 years using trial data, within-trial cost-effectiveness analyses using data collected during the first 24 months and at 36, 48 and 60 months, other published data, expert opinion and population datasets (where appropriate and available).

### Trial oversight

Trial oversight is provided by the Trial Steering Committee (TSC) which comprises an independent chair and three independent members (including one patient representative). Further details can be found in the ‘Acknowledgements’ section. A separate Data Monitoring Committee is not required due to the very low risk associated with the intervention, so this function will be covered by the TSC.

## Discussion

This trial of up to 1400 infants at high-risk of developing atopic eczema will investigate whether daily, all-over application of emollients (of a defined type of formulation) from birth for the first year of life can prevent atopic eczema developing by 2 years of age, and whether any such preventive effects are maintained or are reduced up to the age of 5 years. It will also show whether the intervention can delay the onset of atopic eczema, or whether it alters the severity distribution towards milder disease. The effect on any other atopic conditions associated with atopic eczema (allergic rhinitis, asthma and food allergy) will also be assessed. By assessing the *FLG* genotype of participants, the extent to which any effect of emollients can be modified by filaggrin haploinsufficiency will also be determined. Any differential effect according to *FLG* genotype could be used for a personalised approach to the future use of emollient for the prevention of atopic eczema.

We have taken a pragmatic approach to all aspects of this trial including a limited number of exclusion criteria, interfering as little as possible in the use of the emollient, minimal follow-up and an intention-to-treat analysis. However, as with all pragmatic trials, there are some limitations. Families participating in the trial are likely to be more motivated to use the emollients than the average population. Even so, we may observe a null result due to poor adherence because of the pragmatic nature of the advice to use emollients, whereas the intervention may be effective under conditions that enhance adherence. We have included only families whose child is at higher risk of developing eczema due to family history of atopy, although other groups are planning trials in unselected-for risk populations. Also, we have only offered two emollients in this trial, but there are many others commonly prescribed or purchased by parents. If the trial demonstrates that this relatively cheap and simple intervention is effective in preventing atopic eczema, uptake of the intervention will result in reduced costs for health care providers such as the UK National Health Service. Furthermore, if any effect is extended to the prevention of other atopic conditions then the cost savings could be significantly greater.

The results of the trial will be submitted for publication in peer-reviewed journals and the National Institute for Health Research (NIHR) journal series, and disseminated to health care providers and professional groups including health visitors, midwives, GPs, dermatologists and commissioners. Health care providers and professionals will then have the evidence required to make funding and health care decisions about emollients for preventing atopic eczema. We will inform all trial participants of the results of the main 2-year analysis and 5-year analysis and we will also post our results on the trial register. A variety of media outlets will be used to disseminate the results directly to pregnant women and new parents. Parents are often anxious to know whether their children will develop atopic eczema, especially those with experience of atopic eczema, and are keen to know what they can do minimise the risk. The results of this trial will help inform families whether emollients are an effective prevention strategy.

Other trials of emollients and related interventions for the prevention of atopic eczema are being undertaken throughout the world, and we have formed a collaborative group to undertake a prospectively planned meta-analysis (PPMA) of such studies [44]. Other investigators interested in collaborating in such a PPMA should contact this trial team directly.

